### Confidentiality {27}

As mentioned, only pseudonymized data is stored online with the patient’s consent. In particular, no clear names or personal data are kept online at any point. Also, no data is stored on the application or the end device itself.

The allocation of the clear names to the study data remains in the treating cooperating study sites. Once the study has been completed, the study data are transferred from the secure data center to an offline storage device (external hard drive) and kept in a vault for 10 years according to good clinical practice. The data on the servers is then deleted.

### Plans for collection, laboratory evaluation, and storage of biological specimens for genetic or molecular analysis in this trial/future use {33}

Not applicable.

### Statistical methods

#### Statistical methods for primary and secondary outcomes {20a}

A two-arm evaluation will be performed. In one arm, all patients of the “hip intervention group” and their CG are analyzed. In the other study arm, the evaluation of the “knee intervention group” and their corresponding CG is carried out. A combination of the data from the two study arms is not intended. The statistical analysis is performed separately for patients with TKA and THA by means of mean, median, standard deviation, and quantiles to initially depict the patient collectives and the primary and secondary endpoints descriptively. The Kolmogorov-Smirnov test as well as histograms and QQ-plots are applied to evaluate normal distribution of all continuous variables. Differences at baseline between IG and CG are assessed with Student’s *t*-test for independent variables in case of normally distributed data or with the Mann-Whitney *U* test in case of non-normal distribution. Categorical variables are examined by *χ*^2^ or Fisher’s exact test. If differences are observed, data risk adjustment with logistic regression is applied.

To evaluate outcome differences between the groups, delta values (change scores) are calculated in each group between the adjacent measurement time points (ti-tj, j > i) for each variable. To address our main superiority hypothesis, delta values from baseline to 3 months post-surgery of the IG and CG are statistically examined using Student’s *t*-test for independent variables. Additionally, Cohen’s *d* effect size and its 95% confidence interval will be calculated. Cohen’s *d* is a measure of the effect size for mean difference between two samples regarding interval-scaled variables. Values of *d* = 0.20 represent small, *d* = 0.50 medium, and values from *d* = 0.80 large effect [36]. In the case of non-normally distributed data, the Mann-Whitney *U* test is applied. To investigate differences at the follow-up measurement time points, further *t*-tests were performed. Because of multiple testing, an alpha error correction according to Bonferroni will be applied.

Significant differences between the several measurement times *t*_0_ to *t*_5_ are evaluated with analyses of variance with repeated measures and paired Student’s *t*-test for normally distributed data. The Friedman test and the Wilcoxon test are used in the case of non-normally distributed data.

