### Trial design {8}

The trial is planned as a prospective, randomized, controlled, non-blinded multi-center study to compare “alley” with standard treatment with scope of a superiority study design in two independent indications. Two hundred patients scheduled for THA and 200 patients scheduled for TKA will be independently randomly assigned to the IG or CG. Assessments will be performed at baseline before TJA (*t*_0_), 10 days after TJA (*t*_1_), 1 months after TJA (*t*_2_), 3 months after TJA (*t*_3_), 6 months after TJA (*t*_4_), and 12 months after TJA (*t*_5_).

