### Outcomes {12}

Standardized and self-constructed questionnaires are applied to operationalize the target criteria. After registration with alley, all patients undergo an onboarding process, in which patients complete the medical questionnaires. In total, patients are surveyed at six measurement time points: Baseline before the surgery (*t*_0_) and 10 days after surgery (*t*_1_) as well as 1 (*t*_2_), 3 (*t*_3_), 6 (*t*_4_), and 12 months (*t*_5_) after TJA.

The primary outcome is change from baseline in functional status measured by the Hip Osteoarthritis Outcome Score (HOOS) or Knee injury and Osteoarthritis Outcome Score (KOOS) 3 months after TJA. The statistical analysis will be carried out separately for the two medical indications. Further secondary endpoints of the study are depression, anxiety, physiological, mental, and social health, pain, risk of falling, dispositional optimism and pessimism, patients’ expectation, post-operative complications, satisfaction with treatment, perceived knowledge of the patient about the disease, and health literacy. The secondary endpoints will also be analyzed separately for patients with hip and knee complaints. An overview of the instruments and measurement times is given in Table 2.

**Table 2 Tab2:** Target criteria, assessment instruments, and measurement time points

Target criteria	Assessment instruments	Measurement time points					
		***t***_***0***_	***t***_***1***_	***t***_***2***_	***t***_***3***_	***t***_***4***_	***t***_***5***_

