#### Sample size calculation for patients with osteoarthritis of the hip

The sample size calculation for patients with osteoarthritis of the hip is based on an average change score of 9 points with a standard deviation of ± 15 points in the total score of HOOS observed in other intervention studies after three months [30, 31]. Based on this data available, an effect of 0.6 can be assumed. With a standard α-risk of 0.05 and a statistical power of 0.8 (1 – β), a sample size of *n* = 61 patients in each group is required to obtain significant differences in Student’s *t*-test for independent variables. This number of cases will be enlarged to consider any potential data missing. Due to observed dropout rates of up to 20% [32], exclusion of patients due to errors in data entry (4%) [33], an approximate across-the-board increase due to the risk of complications due to corona the number of patients to be included is increased to achieve the required sample size at the time of measurement 3 months post-surgery. Therefore, *n* = 100 participants and *n* = 100 controls were supposed to be recruited for the THA evaluation group.

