#### Methods for additional analyses (e.g., subgroup analyses) {20b}

In addition to regular statistical analysis group differences will be analyzed regarding sex, age, and secondary diseases. If significant differences are found, risk adjustment will be conducted by logistic regression analysis.

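### Risk adjustment is triggered by baseline differences between randomised arms and uses logistic regression, which does not suit the continuous HOOS/KOOS change score; the plan does not say which result counts

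*Protocol article*

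**What the plan says.** Outcomes {12} sets a continuous endpoint: "The primary outcome is change from baseline in functional status measured by the Hip Osteoarthritis Outcome Score (HOOS" for hip patients, with the KOOS as the knee counterpart, at 3 months after surgery.

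Statistical methods {20a} names the main test without condition on baseline balance: "delta values from baseline to 3 months post-surgery of the IG and CG are statistically examined using Student’s" t-test. It adds that for Cohen's d the "effect size and its 95% confidence interval will be calculated". A switch to Mann-Whitney is foreseen for non-normal data.

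The same section sets the adjustment rule. "Differences at baseline between IG and CG are assessed with Student’s" t-test or, if non-normal, Mann-Whitney; categorical variables get a χ² or Fisher test. Then: "If differences are observed, data risk adjustment with logistic regression is applied".

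Methods for additional analyses {20b} looks at group differences regarding sex, age and secondary diseases and continues: "If significant differences are found, risk adjustment will be conducted by logistic regression analysis".

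The article gives no linear model, no covariate list, no binary HOOS/KOOS responder endpoint and no propensity-score use of logistic regression. It sets no order of precedence between unadjusted and adjusted results.

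**The concern.** There are three linked problems.

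- **Model and outcome do not match.** Logistic regression models a binary variable. For a change score in points, someone would have to choose a cut-point later. The result would be an odds ratio, which cannot be set beside the mean difference and Cohen's d from the main test.
- **The trigger depends on the data.** Under proper randomisation, a test of baseline differences can detect only chance imbalance. It does not show whether a variable predicts outcome, which is the reason to adjust. Whether an adjusted analysis exists, and for which variables, becomes known only once the data are in.
- **There is no hierarchy.** If the rule fires and the two analyses disagree, the plan does not say which one answers the primary hypothesis.

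At stake are prespecification, a clear estimand and precision.

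**Working it through.** **Inputs from the protocol.** Difference 9 points, SD of change 15, so d = 9/15 = 0.6; 61 evaluable per group; 1:1 allocation. The sample size section has: "With a standard α-risk of 0.05 and a statistical power of 0.8". Sidedness is not stated (Trial design {8} says only "with scope of a superiority study design"), so two-sided is assumed.

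**Input assumed.** The correlation ρ between baseline and 3-month score is not in the document; 0.3, 0.5 and 0.7 are tried.

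**1. The plan's own figure.** With d = 0.6, two-sided α 0.05 and power 0.80, the t-test needs 45 per group, not 61. At 61 the power is about 0.91. That mismatch is a separate matter; 61 is used here only as the evaluable number the plan states.

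**2. How often the trigger fires by chance.** For k independent tests at 0.05, the probability of at least one significant result is 1 − 0.95^k.

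| Tests k | Probability |
|---|---|
| 3 (the three factors in {20b}) | 1 − 0.857 = 14% |
| 5 | 1 − 0.774 = 23% |
| 10 (target criteria at t0 in Table 2, apart from sociodemographics) | 1 − 0.599 = 40% |
| 15 | 1 − 0.463 = 54% |

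This applies to hip and knee separately. HOOS/KOOS, VAS pain, DASS and PROMIS-29 overlap in content, so the tests are positively correlated and the true figures would be lower. {20a} says only that differences are observed; {20b} says significant. The 0.05 threshold is therefore carried over to {20a} as a reading.

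**3. What a prespecified linear model gives.** The standard error of the unadjusted difference in change is 15 × √(2/61) = 2.72 points. If both scores have equal variance, ANCOVA on the baseline score multiplies this by √((1+ρ)/2). Approximate power is Φ(9/SE − 1.96).

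| Analysis | SE | Power, formula | Power, simulated |
|---|---|---|---|
| Unadjusted t-test on change | 2.72 | 91% | 90–91% |
| ANCOVA, ρ = 0.3 | 2.72 × 0.806 = 2.19 | 98% | 98% |
| ANCOVA, ρ = 0.5 | 2.72 × 0.866 = 2.35 | 97% | 96% |
| ANCOVA, ρ = 0.7 | 2.72 × 0.922 = 2.50 | 95% | 95% |

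The simulation used normal scores with 61 per group, and for each ρ ran 10,000 trials with no effect and 5,000 with a 9-point effect. The multipliers mean confidence intervals about 19%, 13% and 8% narrower, whatever the sample size.

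**4. Type I error.** In the simulated trials with no effect, ANCOVA rejected in 4.8–5.0%. A rule of using ANCOVA only when the baseline-score test fires rejected in 3.9–4.8%. Overall size is therefore not inflated. In the roughly 5% of trials where the baseline-score test fires, the unadjusted t-test on change rejected a true null in 26%, 20% and 14% (ρ = 0.3, 0.5, 0.7), against 4–5% for ANCOVA. Adjustment for the baseline score is most useful in exactly those trials, and logistic regression does not supply it on the points scale.

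**The case against.** The best defence is that the main analysis is fixed. {20a} ties the superiority hypothesis to the unadjusted t-test, the abstract agrees, and nothing says that a logistic model replaces it. This stands. A reader might infer that chance decides whether the headline result is adjusted, but the text supports less: the adjusted analysis is conditional, and its standing beside the t-test is left open.

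Second, neither section names the dependent variable of the logistic model. A reader might infer that the plan regresses the change score logistically and so can never give a mean difference. That is an inference. A propensity model could lead to an adjusted mean difference, and logistic regression would be ordinary for complications. Neither use is stated, however, and the sentence in {20a} stands unrestricted under a heading covering primary and secondary outcomes.

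Third, a reader might put a figure on the power lost by dichotomising at the median. The protocol names no cut-point, so that loss cannot be charged to it.

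Fourth, {20b} might be faulted for lacking interaction tests. Its heading gives subgroup analyses only as an example, and the text does not claim to test whether the effect differs between patients.

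Finally, covariate lists and model form are often left to an analysis plan. That excuses silence. Here the article names a method, twice, and an analysis plan would have to follow it or contradict it.

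**Conclusion.** The point holds in a limited form. The only adjustment method named does not suit the primary and most secondary outcomes as the article describes them. It is invoked by observed differences between randomised arms, and its rank against the t-test is not given.

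The 14% to 54% chance of a trigger per indication assumes 3 to 15 independent tests at 0.05 and is an upper guide. The gain from a prespecified ANCOVA, about 95–98% against 90–91% power at 61 per group, rests on the protocol's 9 and 15 points and on assumed correlations of 0.3 to 0.7. If all 100 recruited per group were evaluable, unadjusted power would already be about 99%, and the gain would lie mainly in narrower intervals.

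The main t-test is valid under randomisation, and overall type I error is not shown to be inflated. The harm is to prespecification, to the clarity of the adjusted estimand and to precision.

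**What to change.** - Remove baseline tests as a trigger for adjustment in {20a} and {20b}; baseline data can be described by arm without tests.
- For continuous outcomes, replace logistic regression with one prespecified linear model (ANCOVA) per indication. Include the baseline score and a few fixed covariates, such as site, age and sex. Report the adjusted difference in points with its 95% confidence interval; Cohen's d can stay alongside.
- State whether this model or the unadjusted t-test is primary, and give the other as a sensitivity analysis.
- Keep logistic regression for binary outcomes such as complications.
- Interaction tests for sex, age or secondary diseases are optional and, if added, should be labelled exploratory.

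The cost is wording in the protocol and analysis plan, settled before outcome data are examined by arm. No new data are needed: the baseline score and sociodemographic variables are in Table 2, the randomisation list records the hospital, and {20b} already plans to use sex and age.

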### Objectives {7}

Aim of the study is to evaluate the effectiveness of the eHealth application “alley” as an adjuvant intervention to total joint arthroplasty (TJA) as current gold standard of treatment in patients with knee and hip OA scheduled for surgery. In the presented study design, these two indications will be investigated independently of each other. Nevertheless, for both patients’ groups data collection is carried out via “alley” application. Accordingly, the primary outcome is change from baseline in the functional status measured with the total scores of the Hip Osteoarthritis Outcome Score (HOOS) for patients scheduled for total hip arthroplasty (THA) and the Knee injury and Osteoarthritis Outcome Score (KOOS) for patients scheduled for total knee arthroplasty (TKA).

The primary hypothesis is that the pre- and postoperative adjuvant use of the eHealth application “alley” (intervention group, IG) leads to improved functional outcome 3 months after TJA in patients with knee or hip OA compared to their equivalent control group (CG) that did not use the application. In this research, the overall effect of the application as complex intervention will be evaluated as standalone entity. Individual sub-questions on the subject of health literacy or in which format information should be administered to patients are not evaluated. Our secondary hypotheses are that the eHealth application will further improve pain, quality of life, depression and anxiety, optimistic mood, and risk of falling.

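### Change scores for group comparisons are defined between adjacent visits, which conflicts with the change-from-baseline endpoint and leaves the secondary and the 6- and 12-month contrasts unclear

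*Protocol article*

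**What the plan says.** The protocol article, Outcomes {12}, lists six visits: "Baseline before the surgery (*t*_0_) and 10 days after surgery (*t*_1_) as well as 1 (*t*_2_), 3 (*t*_3_), 6 (*t*_4_), and 12 months (*t*_5_) after" surgery. The same section defines the endpoint: "The primary outcome is change from baseline in functional status", on HOOS or KOOS, at 3 months. Objectives {7} adds the secondary aims: "Our secondary hypotheses are that the eHealth application will further improve pain, quality of life", depression and anxiety, mood and risk of falling.

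Statistical methods {20a} then gives a general rule for comparing the groups: "delta values (change scores) are calculated in each group between the adjacent measurement time points (ti-tj, j > i) for each variable". The next sentence turns to the main hypothesis: "delta values from baseline to 3 months post-surgery of the IG and CG are statistically examined using Student’s *t*-test for independent variables". For the other visits the text says only: "To investigate differences at the follow-up measurement time points, further *t*-tests were performed". It adds: "Because of multiple testing, an alpha error correction according to Bonferroni will be applied". The number of tests in that correction is not given.

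The same section plans repeated-measures analysis of variance and paired t-tests over all six visits. They are described as comparisons between measurement times, and no group-by-time term is named.

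**The concern.** The rule on change scores is stated for every variable, but it does not produce the trial's own endpoint. Baseline and 3 months are separated by two visits (10 days and 1 month), so for HOOS and KOOS that change is not an adjacent one. The sentence also disagrees with itself, since its index condition allows any pair of visits in time order.

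For the primary test this is loose wording only. The possible harm lies elsewhere. The secondary hypotheses are about whether the app improves outcomes, and Interim analyses {21b} plans a further main analysis at twelve months. If the adjacent rule governs there, the 12-month comparison asks whether the arms diverge further between 6 and 12 months, and not whether they differ at 12 months. A benefit gained early and kept would then be invisible to the test. Two analysts working from this text could test different 12-month contrasts and reach opposite conclusions.

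**Working it through.** **Inputs.** Visits t0 to t5 (Outcomes {12}); instrument schedule (Table 2); difference of 9 points, SD 15, alpha 0.05, 61 per group, 100 per group to be recruited (Sample size {14}). A two-sided test is assumed because sidedness is not stated.

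**The plan's own figure.** The standardised effect is 9/15 = 0.6, as stated. A two-sided t-test at alpha 0.05 with power 0.80 needs 45 per group (44.6 before rounding), not 61. With 61 per group the power is 0.908. This mismatch is a separate matter and nothing below depends on it. It makes the trial larger than its stated inputs require.

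**Step 1: which contrasts the sentence yields.** Six visits give 5 adjacent pairs: t0–t1, t1–t2, t2–t3, t3–t4 and t4–t5. The index condition alone admits 6 × 5 / 2 = 15 pairs. The primary contrast t0–t3 is among the 15 but not among the 5. The same holds for t0–t4 and t0–t5.

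**Step 2: a sustained benefit under each definition.** Let D(t) be the expected between-arm difference in change from baseline at visit t. Suppose D(t3) = D(t4) = D(t5) = 9.

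- Adjacent change t3–t4: D(t4) − D(t3) = 9 − 9 = 0.
- Adjacent change t4–t5: D(t5) − D(t4) = 9 − 9 = 0.
- Change from baseline at t4 or t5: 9 points.

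With an expected difference of 0, the rejection probability equals alpha whatever the SD or sample size. For change from baseline, the noncentrality of the t-test is 9 / (15 × √(2/n)), which is 3.31 at n = 61 and 4.24 at n = 100. Alpha 0.01 illustrates a Bonferroni correction over five tests, which is an assumption.

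| Contrast at 6 or 12 months | n per arm | Alpha 0.05 | Alpha 0.01 |
|---|---|---|---|
| Adjacent change | 61 or 100 | 0.05 | 0.01 |
| Change from baseline | 61 | 0.908 | 0.755 |
| Change from baseline | 100 | 0.988 | 0.949 |

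SD 15 is documented for the 3-month change only. Its use at 6 and 12 months is an assumption.

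**Step 3: a benefit that builds up gradually.** If the 9 points accrue evenly over t0–t1, t1–t2 and t2–t3, each interval carries 3 points. The protocol gives no SD for a single interval, so a range is needed (61 per arm, two-sided 0.05):

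| Assumed SD of one interval | Power per interval |
|---|---|
| 15 | 0.195 |
| 12 | 0.28 |
| 10 | 0.38 |
| 8.7 (15/√3, independent increments) | 0.48 |

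All are well below the 0.908 for the cumulative change.

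**Step 4: the rule against Table 2.** The patient experience questionnaire (PEQ) is collected only at t2 and t3, so its only adjacent change is the shift in satisfaction from 1 to 3 months, not a difference in satisfaction between the arms. Post-operative complications have no t0. Optimism and risk of falling skip t1 and t2, so their adjacent change ending at 3 months is t0–t3, whereas for pain, DASS and PROMIS-29 it is t2–t3. One rule therefore gives different contrasts at the same visit.

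**The case against.** The strongest reply is that the text can be read sensibly. The primary contrast is named in the very next sentence and agrees with the abstract, the objectives and the outcomes section, so no analyst would run the wrong primary test. That stands in full.

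The sentence on follow-up visits does not name the variable tested. It comes directly after the baseline-to-3-month test and speaks of differences at the visits, which suggests the same kind of contrast later on, or a comparison of levels. The index condition also permits t0–t4 and t0–t5. This stands too. A reader might infer that the 6- and 12-month comparisons are blind to a sustained effect, but the protocol does not commit itself to that. It follows only if *adjacent* is taken literally. Descriptive statistics are also planned, so a lasting difference could still be seen.

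A reader might also make something of the sign, since the notation puts the earlier visit first and an increase would come out negative. That changes no two-sided between-arm test and may only denote an interval.

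Finally, an article may leave the contrast for each secondary instrument to a fuller document. That would answer a missing detail. It does not answer a rule that is stated for each variable and does not fit the endpoint.

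**Conclusion.** The point holds as a badly fixed rule for secondary outcomes and later visits. The definition of change scores contradicts its own index and does not yield the change-from-baseline endpoint. The primary analysis is unaffected.

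The size of the problem depends on the reading. Under the literal adjacent rule, and if a 9-point benefit is reached by 3 months and kept, the 6- and 12-month tests reject with probability alpha, against about 0.91 for change from baseline (SD 15, 61 per arm, two-sided 0.05). Under the wider reading allowed by the index there is no such loss. The wording conflict is certain and the loss of power is conditional. Because the text does not say which reading applies, the choice could be made after the data are seen. That is reason enough to settle it.

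**What to change.** Replace the sentence on change scores with a definition of change as follow-up minus t0 at every visit (t1 to t5). State that the arms are compared on this change, or on the baseline-adjusted level, for the primary and the secondary outcomes at each follow-up. For outcomes without a t0 value, such as PEQ and post-operative complications, compare the observed post-surgery values directly. Keep changes between adjacent visits as descriptive only, outside the Bonferroni family.

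The cost is a short rewording in the protocol and, if one exists, the analysis plan. No data, visits or patients are added. If adjacent-interval tests were intended, there will be fewer tests to correct for.

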### Assignment of interventions: allocation

#### Sequence generation {16a}

A 1:1 randomization has been conducted, assigning patients to either CG or IG for THA or TKA, respectively. For this purpose, two randomization lists have been created using Excel random number generator, creating separate lists for THA and TKA. These lists contained a predefined identification code for each indication, which was randomly assigned to the IG or CG. If patients agreed to participate, they were assigned to this list and thus received a unique identification code. This personal code serves as login for the “alley” application. As the randomization list was a shared online document for all study sites, simultaneous double submissions had to be avoided. For this reason, block randomization has been used for blocks of 50 patients. This means that each of the eight study sites is allocated to a fixed slot of 50 patients on the randomization list. During patient recruitment, these slots are successively filled. If more than 50 patients are to be recruited, new slots can be released at the end of the list. The randomized allocation of patients to either IG or CG allows minimizing the inclusion of patients with strong affinity for using digital applications in the IG. Randomization will ensure an equal distribution of patients.

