## Strengths and limitations

The present study will have clear strengths and weaknesses. Methodologically, the study is designed as a prospective, randomized, controlled, multi-center trial with clear inclusion and exclusion criteria. Although the basic conditions of the patients are similar in all clinics, it cannot be excluded that clinic-internal processes or procedures influence the change in outcome (e.g., different surgical accesses, special pain management within a clinic, etc.). Since the study examined the effectiveness under everyday conditions, it could not be controlled whether patients in the IG read the patient-educational information provided by the “alley ortho companion” app or whether patients in the CG did consume additional information from the Internet or brochures in preparation for TJA. However, this type of study design increases the external validity, which improves the generalizability of the study results. Concurrently, it should be noted that there are certain limitations regarding the transferability of the results to the general target group of the application. The external validity could be distorted by the incentive of 150 EUR per patient. We cannot exclude the possibility that the patients have engaged with the app particularly intensively for this reason. Nevertheless, we believe that differences in the HOOS and KOOS score between the IG and CG can still be directly attributed to the intervention due to the randomized controlled trial design. Another limitation is that the use of a digital application requires the ownership of a mobile device, the ability to handle the device, and the ability to handle the app itself. Due to the advanced age of the patients with osteoarthritis, some individuals could be systematically excluded from the effects of the intervention. For these patients, the most important core information from the alley application could be provided to as written handout or brochure. To systematically examine this potential third study arm, the sample size would have had to be highly increased, which was not possible for logistical and economic reasons in the current design.

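### Primary analysis is an unadjusted change-score t-test with a data-driven switch to Mann-Whitney; one prespecified ANCOVA on baseline score and site would be at least as precise and would fix what is tested

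*Protocol article*

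**What the plan says.** All references are to the protocol article.

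- **Default test.** Statistical methods {20a}: for the main hypothesis, "delta values from baseline to 3 months post-surgery of the IG and CG are statistically examined using" Student's t-test, with Cohen's d and its 95% confidence interval in addition. Hip and knee are analysed separately.
- **Switch.** Same section: "In the case of non-normally distributed data, the Mann-Whitney *U* test is applied". The Kolmogorov-Smirnov test, histograms and QQ-plots "are applied to evaluate normal distribution of all continuous variables". No threshold is given, and no rule for the case where the three disagree.
- **Adjustment.** Same section, after the baseline comparison of the arms: "If differences are observed, data risk adjustment with logistic regression is applied". Additional analyses {20b} repeats this for sex, age and secondary diseases: "If significant differences are found, risk adjustment will be conducted by logistic regression analysis".
- **Site.** Sequence generation {16a}: "each of the eight study sites is allocated to a fixed slot of 50 patients on the randomization list". Strengths and limitations: "it cannot be excluded that clinic-internal processes or procedures influence the change in outcome". No site term appears in the primary test.

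**The concern.** Three features of the primary analysis are fixed in a weak form.

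1. **Baseline.** A change score forces the coefficient of baseline to be exactly 1. ANCOVA estimates that coefficient and so normally leaves less residual variance. The baseline HOOS/KOOS is scheduled for every patient at t0, so the information is to hand.
2. **The switch.** The t-test compares mean changes; Mann-Whitney compares ranks. If the normality check triggers the switch, the p-value no longer belongs to the mean difference that Cohen's d describes. Hip and knee could end with different tests.
3. **The remedy for imbalance.** It is triggered by baseline tests, and it names a model for binary outcomes although the primary outcome is continuous. As written it cannot adjust the HOOS/KOOS comparison.

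At stake are the width of the interval for the primary effect and the certainty, before the data are seen, of which quantity the primary p-value refers to.

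**Working it through.** **Inputs from the protocol article.** Difference 9 points, SD 15, hence d = 9/15 = 0.6; alpha 0.05; power 0.80; 61 evaluable and 100 recruited per arm and indication (Sample size {14}); eight sites (Study setting {9}). Sidedness is not stated; two-sided is assumed.

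**Assumed inputs.** The correlation rho between baseline and 3-month score, and the ratio k of the 3-month SD to the baseline SD, are not given. Ranges are shown.

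**The plan's own figure.** For a two-sample t-test with d = 0.6, alpha 0.05 and power 0.80, the exact calculation gives 44.6, so 45 per arm two-sided (36 one-sided), not 61. A design effect is mentioned without a value; 61/45 = 1.36 would be needed. That discrepancy is a separate point. Here 61 is taken as the evaluable number. Power of the planned t-test is then 0.908 at 61 per arm and 0.988 at 100.

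**Variance of ANCOVA relative to the change-score test.** Take the baseline variance as 1 and the 3-month variance as k².

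- Change score: 1 + k² − 2·rho·k
- ANCOVA residual: k²(1 − rho²)
- Ratio: k²(1 − rho²) / (1 + k² − 2·rho·k)
- Denominator minus numerator: 1 − 2·rho·k + rho²k² = (1 − rho·k)², which is never negative

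In large samples ANCOVA is therefore never less precise, and it ties only when rho·k = 1. With equal SDs (k = 1) the ratio reduces to (1 + rho)/2.

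**Equal SDs, d = 0.6.** The effective effect size is 0.6/√ratio.

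| rho | variance ratio | SE reduction | n per arm for 80% power (t-test: 45) | power at 61 per arm (t-test: 0.908) |
|---|---|---|---|---|
| 0.3 | 0.65 | 19% | 30 | 0.983 |
| 0.5 | 0.75 | 13% | 34 | 0.967 |
| 0.7 | 0.85 | 8% | 39 | 0.946 |
| 0.9 | 0.95 | 2.5% | 43 | 0.921 |

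**Unequal SDs.**

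- k = 1.25, rho = 0.8: 0.5625/0.5625 = 1.00, no gain.
- k = 1.25, rho = 0.5: 1.1719/1.3125 = 0.89.
- k = 0.8, rho = 0.5: 0.48/0.84 = 0.57.

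**Cost in degrees of freedom.** At 61 per arm the t-test has 122 − 2 = 120. Baseline (1) and seven site terms use 8, leaving 112. The two-sided critical value moves from 1.980 to 1.981, and the powers above change by less than 0.001.

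**The switch.** A simulation of 5,000 trials per scenario, 61 per arm, applied a 5% Lilliefors-type check in each arm and then the t-test or Mann-Whitney. It stands in for the plan's check, which has no threshold.

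| data under the null | switched to Mann-Whitney | two-stage type I error |
|---|---|---|
| normal | 9% | 0.050 |
| skewed (gamma, shape 4) | 72% | 0.050 |
| heavy-tailed (t, 5 df) | 42% | 0.049 |

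The switch is a realistic event, but it did not inflate the error rate in these scenarios. In the same t-test-only runs the error was 0.048 to 0.049, so at this sample size the t-test did not need rescuing.

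**The case against.** The strongest reply is that the planned test is sound. Under individual randomisation an unadjusted change-score t-test is unbiased, and leaving site out does not invalidate it. On the plan's own effect size it already has about 91% power at 61 per arm. Taking 20% dropout and 4% data-entry exclusions off 100 leaves about 76 per arm, where power is 0.957 and ANCOVA adds only 0.8 (rho 0.9) to 3.8 (rho 0.3) percentage points. All of this stands, and it limits the point to precision and prespecification.

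Several stronger readings are tempting, and the document does not support them:

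- *Baseline is ignored.* It is not: the change score subtracts it, and a conditional adjustment is planned, though with an unsuitable model.
- *The plan expects site to affect outcome.* It says only that this cannot be ruled out, and it gives a logistical reason for the site slots, namely avoiding double entries in a shared list.
- *The primary hypothesis is left open.* Hypothesis, endpoint, time point and default test are all stated in advance, and the analyst is blinded. Only the fallback depends on the data.
- *The switch inflates type I error.* The simulation gives no support for this.
- *ANCOVA is bound to save a quarter or more of the patients.* That needs rho of 0.5 or below with equal SDs; the document gives neither.

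It could also be said that covariates belong in an analysis plan that is not shown. That would answer an omission. Here the article itself names the test, the switch and the logistic regression, so these choices can be assessed as written.

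**Conclusion.** The point holds as a weakness of precision and prespecification in a valid primary analysis. With equal SDs, ANCOVA removes from 35% (rho 0.3) to 5% (rho 0.9) of the change-score variance. The gain can fall to nothing when rho times the SD ratio equals 1, and in large samples it cannot be negative. These sizes rest on the assumed rho and k and, for power, on two-sided testing at d = 0.6 with 61 per arm.

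Two parts of the conclusion need no assumption about rho: a switch to Mann-Whitney would change the quantity tested, and logistic regression is not a model for a continuous change score. The change is worth making because it is nearly free.

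**What to change.** For each indication, before 3-month outcomes are examined by arm:

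1. Make the primary analysis one linear model of the 3-month HOOS or KOOS total on arm, baseline total and site, used whatever the normality check shows.
2. Report the adjusted mean difference in points with its 95% confidence interval, plus Cohen's d, and state which SD standardises d.
3. Keep the change-score t-test and Mann-Whitney as labelled sensitivity analyses.
4. Delete the conditional logistic-regression adjustment for the primary outcome in {20a} and {20b}. If sex, age or secondary diseases are wanted as covariates, name them in advance in a linear model.

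The cost is wording and about 8 of 120 degrees of freedom. No new data are needed: the baseline score is collected at t0, and the shared trial list has a field for the hospital (Concealment mechanism {16b}).
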